**Table 2 Tab2:** **Home exercise program protocol**

Maximum of 6 exercises (with progression as appropriate)			
	2 knee extensor strengthening exercises		
	1 hip abductor strengthening exercise		
	1 hamstring strengthening exercise		
	1 calf strengthening exercise		
	1 other exercise chosen based on assessment findings		
**1. Quads strengthening (each program must include 2 exercises)**			
**Knee extension**	Non weight-bearing	A. Seated knee extension (with resistance) with 5 second hold	**Indications:** suggested as an initial exercise
			**Progression:** Increase cuff weight or theraband resistance – red through to black
			**Simplification:** eliminate weight or see 1B
	Non weight-bearing	B. Inner range quads over roll (with resistance) with 5 second hold	**Indications:** Usually only required when any flair ups with seated knee extension (1A)
			**Progression:** Use appropriate level of ankle cuff weight
			**Simplification:** eliminate weight if flare up
**Sit-to-stand**	Weight-bearing	C. Sit to stand without using hands	**Indications:** suggested as an initial exercise
			**Progression:** lower chair height, hover above the seat without touching down, more weight on affected leg, slit leg position (affected leg closer to seat)
			**Simplification:** use hands
**Steps**	Weight-bearing	D. Step-ups	**Indications:** suitable progression from sit to stand (1C)
			**Progression:** Increase step height, hold extra weight (in hands or backpack)
			**Simplification:** sit to stand (1C)
	Weight-bearing	E. Forward touchdowns from a step	**Indications:** suitable progression from step-ups (1D)
			**Progression:** Increase step height, hold extra weight (in hands or backpack), don’t touch down
			**Simplification:** step-ups (1D)
**Partial squats**	Weight-bearing	F. Partial wall squats	**Indications:** suitable progression from sit to stand (1C)
			**Progression:** Increase to 5 sec hold, more weight on study side)
			**Simplification:** if find flare/problematic step back to sit to stand (1C)
**2. Hip abductor strengthening (1 exercise)**			
**Standing hip abduction**	Non weight-bearing	A. Side leg raises in standing	**Indications:** suggested as an initial exercise
			**Progression**: Increase cuff weight or theraband resistance – red through to black
			**Simplification:** eliminate weight
**Side stepping**	Weight-bearing	B. Crab walk with resistance band	**Indications:** good progression from standing leg side raises (2A)
			**Progression:** Increase theraband resistance – red through to black
			**Simplification:** side leg raises in standing (2A)
**Standing hip abduction**	Weight bearing	C. Wall push standing on study leg	**Indications:** good progression from crab walking (2B) and for variety at final session
			**Progression:** Increase step height. Hold extra weight (in hands or backpack)
			**Simplification:** If unable to tolerate static standing on joint then avoid and use 2B or 2A. Precaution in those with increased varus.
**3. Hamstring strengthening (1 exercise)**			
**Standing knee flexion**	Non weight-bearing	Standing over bench knee curls with weight	**Progression:** Increase cuff weight or theraband resistance – red through to black
			**Simplification:** eliminate weight
**4. Calf strengthening (1 exercise)**			
**Standing plantar-flexion**	Weight-bearing	Double heel raises	**Progression:** single heel raises, raises from the edge of a step
**5. Others (1 exercise if appropriate)**			
**Knee ROM**	Weight bearing	A. Deep squats holding onto a bench/chair	**Progression:** increase squat depth
**Hip ROM**	Weight bearing	B. Deep lunges holding onto back of chair/bench	**Progression:** increase lunge depth
**Hip extensors**	Weight-bearing	C. Bridging	**Progression:** split leg bridge, single bridge with a hold, bridging one leg

Using the Internet to mediate learning, the physiotherapist will begin each participant’s exercise program by selecting exercises and prescribing dosages based on findings from an initial assessment of the participant’s pain and perceived level of effort during performance of an exercise. The participant will learn each exercise by observing as the physiotherapist demonstrates the exercise and then performing it under the physiotherapist’s supervision.

The physiotherapist will perform a brief assessment at each physiotherapy session to ascertain any adverse effects that may have occurred with home exercises and check quality and form of exercise performance. Progression of exercises will be provided by varying the type of exercise as well as the number of repetitions, load or degree of difficulty within an exercise. The prescribed resistance will aim to approximate a 10-repetition maximum level and a patient-rated level of effort experienced during each strengthening exercise of at least 5 out of 10 (hard) on a modified Borg Rating of Perceived Exertion CR-10 scale designed specifically for strengthening exercise [51].

In order to minimise burden of exercise, only the study knee will be the focus of treatment and evaluation. If participants have bilateral symptoms, the physiotherapist may choose exercises that are performed in weight-bearing on both legs simultaneously to achieve bilateral strength gains within the constraints of the treatment protocol.

Although some discomfort is expected during the exercise intervention, any exercise-related pain should subside to usual levels by the next day with no increase in knee swelling following the exercise session. Participants will be taught how to determine whether pain levels are acceptable or not during and for a short time after the exercises. If a specific exercise is aggravating the participant’s pain, then the physiotherapist will reduce the resistance, dosage and/or level of challenge within the exercise until the pain flare settles or change the exercise completely if it remains pain provoking.

#### Treatment fidelity

Eight experienced musculoskeletal physiotherapists (4 female, 4 male) in 7 locations around metropolitan Melbourne and regional Victoria have been selected and trained to deliver the study exercise intervention. They have an average of 16 years (minimum 3 years, maximum 28 years) of clinical experience treating musculoskeletal disorders. They attended a full-day training course in Melbourne conducted by the researchers on February 22nd 2014 and were provided with a detailed intervention manual. Training included information about study procedures and protocol, exercise delivery, progression and monitoring. As therapists are encouraged to support and reinforce pain coping skills taught on PainCOACH, they also received background information, exposure and education about those skills so they can be integrated into the exercise program and daily life. Regular telephone/Skype meetings between the physiotherapists and a member of the research team will be held throughout the study. Physiotherapists will complete standardised treatment notes for each participant’s individual treatment session and return these via an online survey within 48 hours of the session appointment. Treatment fidelity will be assessed using a treatment check list applied to key points within the treatment notes.

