### Sample size

The primary endpoints of the trial are between-group (PCST + Ex group versus the educational control group) differences in change in knee pain on walking (NRS) and change in physical function (WOMAC). Moderate between-group treatment effects of around 0.5 have previously been reported for pain and function following individual exercise programs in people with knee OA [13, 67]. Therefore, to enable detection of at least a 0.5 effect size between groups in either pain or function in a two-arm trial with 80% power, a significance level at 0.05 and allowing for 15% attrition rate, we will recruit 74 participants in each group or a total of 148 participants.

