### Data and statistical analysis

A biostatistician (MPS) blinded to group allocation will analyse data. Main comparative analyses between groups will be performed using intention-to-treat. This analysis will include all participants who have missing data and those who do not fully adhere to the protocol. Demographic characteristics, as well as baseline scores on primary and secondary outcome measures, will be inspected to assess baseline comparability of treatment groups. These variables will also be examined for those participants who withdraw from the study and those who remain. Descriptive statistics will be presented for each group as the mean change (standard deviation, 95% confidence intervals) in the outcomes from baseline to each time-point. For continuous outcomes differences in mean change will be compared between groups using linear regression random effects modelling adjusted for baseline values of the outcome. Proportional odds models will compare improvement between groups based on perceived ratings of change as well as the proportion in each group who attain the minimum clinical important difference (MCID) for pain and function. The MCID to be detected in OA trials is a change in pain of 1.8 units (out of 10) [54] and change in function of 6 points (out of 68) [57]. Model diagnostic checks will utilise residual plots. Similar regression models for binary and ordinal outcome measures will use random effects logistic and proportional odds models, respectively. We will also perform a per protocol analysis as appropriate.

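### Physiotherapists treat only the PCST + Ex arm, yet the sample size makes no allowance for therapist clustering and the random effect in the analysis model has no named grouping unit

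*Protocol article*

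**What the plan says.** The Treatment fidelity section of the protocol article states that "Eight experienced musculoskeletal physiotherapists (4 female, 4 male) in 7 locations around metropolitan Melbourne and regional Victoria have been selected and trained". The PCST + Ex condition section gives each participant in that arm seven video consultations and an individually prescribed home programme. The Education control condition section gives controls a link to information sheets and no therapist. The Treatment adherence section refers to the treating physiotherapist in the singular, which points to one therapist per participant.

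The Sample size section sets out "to enable detection of at least a 0.5 effect size between groups in either pain or function in a two-arm trial with 80% power", with "a significance level at 0.05", and continues: "allowing for 15% attrition rate, we will recruit 74 participants in each group or a total of 148 participants". It has no ICC or design effect.

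The Data and statistical analysis section says that, for continuous outcomes, "differences in mean change will be compared between groups using linear regression random effects modelling adjusted for baseline values of the outcome". Random effects models are also named for binary and ordinal outcomes. The unit that carries the random effect is not given for any of them. The Discussion describes the study as adequately powered for its primary outcomes.

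**The concern.** The physiotherapist chooses exercises from a list, sets and progresses the load, responds to pain flares and reinforces coping skills. Clinical experience in the group ranges from 3 to 28 years. Participants of the same physiotherapist may therefore have more similar walking pain and WOMAC function than participants of different ones, and this can arise in one arm only.

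Two statements in the article are affected. The 80% power treats all participants as independent. The model, read in the natural way as a participant effect for outcomes repeated at 3 and 9 months, contains no therapist variation. On that reading, the confidence intervals for both primary outcomes are too narrow if the therapist ICC is positive. If a therapist effect was intended instead, an ordinary random intercept has no defined cluster for the control half of the sample. The analyst would then have to decide how to treat controls, and that decision affects the standard error.

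**Working it through.** **Inputs from the article.** Effect size 0.5 SD, 80% power, alpha 0.05 (taken as two-sided, which reproduces the stated number), 15% attrition, 74 per arm, eight physiotherapists.

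**Assumptions.** Therapist ICC of 0.02, 0.05 or 0.10 (the article gives none); equal caseloads; equal total variance in the two arms; normal approximation.

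**Step 1: reproduce the plan's figure.** n per arm = 2 × ((1.96 + 0.842)/0.5)² = 62.8. Allowing for attrition, 62.8/0.85 = 73.9, so 74 per arm and 148 in total. The stated number is reached with no design effect. Analysed per arm: 74 × 0.85 = 62.9, which gives power of 80.1%. There is no spare margin.

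**Step 2: cluster size.** m = 62.9/8 = 7.86 analysed participants per physiotherapist.

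**Step 3: clustering in one arm.**
- Design effect in the PCST + Ex arm: DE = 1 + (m − 1) × ICC.
- Variance of the difference, in SD units: (1 + DE)/62.9, against 2/62.9 if therapist is ignored.
- Ratio of true to model standard error: R = √((1 + DE)/2). Understatement = 1 − 1/R.
- Actual type I error of a nominal 5% test: 2 × (1 − Φ(1.96/R)).
- Power with the correct standard error: Φ(0.5/√((1 + DE)/62.9) − 1.96).

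For ICC 0.05: DE = 1 + 6.86 × 0.05 = 1.34; R = √(2.343/2) = 1.082; understatement = 1 − 1/1.082 = 7.6%; type I error = 2 × (1 − Φ(1.811)) = 7.0%; power = Φ(0.5/0.193 − 1.96) = Φ(0.631) = 73.6%.

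| Assumed ICC | DE | R | SE understated by | Type I error if therapist ignored | Power, no baseline adjustment |
|---|---|---|---|---|---|
| 0 | 1.00 | 1.000 | 0% | 5.0% | 80.1% |
| 0.02 | 1.14 | 1.034 | 3% | 5.8% | 77.4% |
| 0.05 | 1.34 | 1.082 | 8% | 7.0% | 73.6% |
| 0.10 | 1.69 | 1.159 | 14% | 9.1% | 67.7% |

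**Step 4: baseline adjustment.** The model adjusts for the baseline score. With an assumed baseline–follow-up correlation of 0.5 (not in the article), the variance is multiplied by 1 − 0.5² = 0.75. Applying the same ICC to the adjusted outcome, power at ICC 0.02 / 0.05 / 0.10 is about 88% / 85% / 80%. R does not change, so neither does the type I error of an analysis that omits therapist.

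Unequal caseloads, and the few degrees of freedom that eight physiotherapists provide, would make the figures somewhat worse. Neither is included above.

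**The case against.** The strongest reply concerns the model. A reader might infer that it excludes therapist and that its standard errors are therefore too small. The article does not support that. It specifies random effects without saying for what. Conclusions rest on change to 3 months, and if that contrast were analysed alone, with one value per participant, a participant effect could not be separated from residual error, so the random effect would have to be for something else. A separate analysis plan may define it, and an article commonly leaves such detail to that plan. This stands: the harm is conditional on therapist being omitted and on a positive ICC.

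A second tempting inference is that the trial is underpowered. That is not shown either. The planned baseline adjustment can offset the loss, although the correlation of 0.5 behind those figures is itself an assumption.

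Third, therapist variation may be small. The exercise list is restricted, training and a manual are provided, fidelity is checked, and the PainCOACH component is automated. At an ICC of 0.02 the standard error is only about 3% too small. This is fair, and the article offers nothing to support 0.10 in particular.

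Fourth, with eight physiotherapists the variance component is imprecise, and a statistician could prefer the therapist term as a sensitivity analysis. The imprecision is real, but it is a reason for small-sample degrees of freedom rather than for leaving the term out.

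The objection does not remove the sample-size point. The article gives a complete derivation that omits a feature the same article describes, and a later analysis plan would not alter that calculation.

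**Conclusion.** The point holds in conditional form and should be addressed. It is established that physiotherapists treat one arm only, that 148 contains no allowance for therapist clustering, and that the random effect is undefined and therapist unmentioned. If the random effect is for participant only and the therapist ICC is positive, the standard errors of both primary comparisons are too small. Over the assumed ICC range of 0.02 to 0.10 the understatement is about 3% to 14% and type I error is about 5.8% to 9.1%. Before baseline adjustment, power is about 77% down to 68%.

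The main risk is therefore confidence intervals that are too narrow rather than a lack of power. The size depends on an ICC that the article does not give and on equal caseloads, for which it states no assignment rule.

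**What to change.** - **Data and statistical analysis:** state what the random effect represents. Add a physiotherapist random effect in the PCST + Ex arm only, with controls treated as unclustered. Use Satterthwaite or Kenward-Roger degrees of freedom for the two continuous primary outcomes, and report the estimated ICC.
- **Sample size:** state that the 80% assumes no therapist clustering and no baseline adjustment. Give power over a range of ICCs, with the baseline correlation assumed for any adjusted figures. Keep 148.
- **Data capture:** confirm that the treating physiotherapist's identity is recorded with the session notes. This is likely, because physiotherapists submit a note for each session, but the article does not list it as a field.

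The cost is some wording and one extra variance term. No added recruitment is needed, and no new data if identity is already captured. The confidence interval will be slightly wider at small ICCs (at 0.10 the standard error rises by about 16%, before the degrees-of-freedom penalty), and the variance component will be imprecisely estimated from eight physiotherapists.

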### Descriptive data

Age, gender, duration of knee symptoms, previous treatments, medical history, and medication use will be obtained at baseline by an online questionnaire.

### Outcome measures

The outcome measures are summarised in Table 3. Primary outcomes will be measured at baseline, 3 months and 9 months. Conclusions regarding treatment effectiveness will be evaluated based on changes in primary outcome measures from baseline to 3 months. Our two primary outcomes, which are recommended as valid measures of pain and physical function for knee OA [52], are:

**Table 3 Tab3:** **Summary of outcome measures and time points**

Primary outcome measures	Data collection instrument	Collection points
Average walking pain in past week	11-point numeric rating scale	0, 3^¥^, and 9 months
Physical function in past 48 hours	WOMAC osteoarthritis Index physical function subscale	0, 3^¥^, and 9 months
**Secondary outcome measures**		
Pain in past 48 hours	WOMAC osteoarthritis Index pain subscale	0, 3 and 9 months
Perceived change overall	7-point ordinal scale	3 and 9 months
Perceived change in pain	7-point ordinal scale	3 and 9 months
Perceived change in function	7-point ordinal scale	3 and 9 months
Health-related quality of life	Assessment of Quality of Life questionnaire (AQoL2)	0, 3 and 9 months
Self-reported psychological measures	Arthritis self-efficacy scale	0, 3 and 9 months
	Coping Strategies questionnaire (CSQ)	0, 3 and 9 months
	Pain Catastrophizing Scale (PCS)	0, 3 and 9 months
**Other measures**		
Adherence to intervention	Number of physiotherapy sessions attended	During intervention
	Weekly home exercise log books	During intervention
	PainCOACH module completion	During intervention
	PainCOACH practice via COACHTrack/ log books	During intervention
	Home exercises - 11-point numeric rating scale	3, 6 and 9 months
	Frequency of home exercise sessions previous 2 weeks	3, 6 and 9 months
	Frequency of pain coping skills in previous 2 weeks	3, 6 and 9 months
	Educational material accessed in previous 3 months	3, 6 and 9 months
Adverse events and harms	Questionnaire	3, 6 and 9 months
Health cost data	Questionnaire	9 months
Descriptive information	Questionnaire	0 months
Medications and co-interventions	Questionnaire	0, 3, 9 months
Treatment benefit expectations	5-point ordinal scale	0 months
**Process measures**		
Treatment satisfaction	Questionnaire	3 months
Appropriateness of the intervention	Program (System) usability scale	3 months

^¥^Primary outcomes and primary time point.

#### Knee pain on walking measured by an 11-point NRS

Average knee pain on walking over the past week will be self-reported using an 11-point numeric rating scale (NRS) (0 = no pain, 10 = worst pain possible). This measurement is reliable and valid in OA populations [53]. The minimum clinically important difference to be detected in OA trials has been defined as a change in pain of 1.8 units (out of 10) [54].

#### Physical function measured by the function subscale of the WOMAC

Physical function will be measured by the WOMAC Osteoarthritis Index (Likert version 3.1) [55]. This is a disease-specific self-report questionnaire with extensive evidence of validity, reliability and responsiveness in OA populations [56]. The physical function subscale contains 17 questions (each answered on a Likert scale where 0 = no dysfunction and 4 = extreme dysfunction) and has a total score ranging from 0 (no dysfunction) to 68 (maximum dysfunction). The minimum clinically important difference to be detected in OA trials has been defined as a change in function of 6 points (out of 68) [57].

Our secondary outcome measures, which will collected at baseline, 3 and 9 months, unless otherwise indicated below, include:

#### Participant-perceived response to treatment measured on 7-point scales

Participants will rate their perceived change in a) pain, b) physical function and c) overall condition on a seven-point ordinal scale (1-much worse to 7-much better) at 3 and 9 months. This scale will be used as an external criterion for comparison with changes in scores of other outcomes [58]. Measuring participant-perceived change using a rating of change scale has been shown to be a reliable and clinically relevant method of identifying improvements that are truly meaningful from the individual perspective [59]. Participants who report that they are moderately better and above will be classified as improved.

#### Knee pain measured by the WOMAC pain subscale

Knee pain will also be captured using the WOMAC pain subscale, which contains five questions, each answered on a Likert scale where 0 = no pain and 4 = extreme pain. It has a total score ranging from 0 (no pain) to 20 (maximum pain) [55].

#### Health-related quality of life measured by the Assessment of Quality of Life (AQoL)

The AQoL questionnaire (version AQoL-II) contains 20 questions that cover six dimensions of health-related quality of life including independent living, social relationships, physical senses, coping, pain and psychological wellbeing. Responses to each question are answered on 5-point scale. Scores range from -0.04 (worst possible health-related quality of life) to 1.00 (full health-related quality of life). The AQoL-II has strong evidence of validity and responsiveness [60, 61]. A clinically important difference in health-related quality of life has been defined as a change of 0.04 AQoL units [62].

#### Self-efficacy for pain and function measured by the arthritis self-efficacy scale

Self-efficacy for pain management and its effects on function will be measured with the Arthritis Self-Efficacy Scale [63], which assess confidence for managing pain (5 questions) and physical function (9 questions) on a 10-point NRS (where 1 = very uncertain and 10 = very certain). Responses are averaged so that higher scores indicate greater self-efficacy. This scale is reliable and valid in OA populations [63].

